## Methods and analysis

### Study design

This is a multicenter, parallel-group, randomized controlled, open-label trial (Fig. 1). The study has been approved by the Medical Ethics Committee of the Jiangsu Hospital of Integrated Traditional Chinese and Western Medicine and registered in the Chinese Clinical Trial Registry (ChiCTR2100043770). This study will be conducted at Jiangsu Hospital of Integrated Traditional Chinese and Western Medicine, Suzhou Hospital of Traditional Chinese Medicine, Suqian Hospital affiliated with Xuzhou Medical University, Xuzhou Mineral Group General Hospital, Xiamen Hospital of Traditional Chinese Medicine, and Nanjing Jiangning District People’s Hospital. A total of 184 participants will be enrolled and randomly assigned to the canagliflozin and metformin treatment groups.

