#### Exclusion criteria (during screening, those who meet any of these criteria will be excluded)

(1) Severe diabetic complications include severe diabetic nephropathy (estimated glomerular filtration rate (eGFR) of < 60 mL/min/1.73 m^2^), diabetic foot (Wagner grade 2 or above) and diabetic retinopathy (with fundus hemorrhage affecting vision).

(2) Severe organ diseases or other severe primary diseases such as liver and kidney dysfunction, heart failure, cerebral infarction, and malignant tumors.

(3) Severe cognitive dysfunction and unclear language expressions.

(4) Mental illness.

(5) Severe chronic infection.

(6) History of acquired immunodeficiency syndrome and drug abuse.

(7) Pregnant or lactating women.

(8) Participation in another clinical trial.

(9) Blood donation or blood loss of ≥ 400 mL within 4 weeks before screening or recipient of blood transfusion.

(10) Fasting plasma/serum glucose > 15 mmol/L.

(11) Alanine aminotransferase ≥ 2.5 × upper limit of normal(ULN).

(12) Total bilirubin ≥ 1.5 × ULN.

(13) Hemoglobin ≤ 100 g/L and neutrophils < 1.5 × 10^9^/L.

(14) Renal injury (eGFR < 60 mL/min/1.73 m^2^ or serum creatinine ≥ 2.5 × ULN or on kidney dialysis).

(15) Blood thyroid-stimulating hormone level beyond the normal range and has clinical significance, as assessed by researchers.

(16) Parathyroid hormone > 1.5 × ULN.

(17) Myocardial enzyme spectrum (creatine kinase and creatine kinase isoenzyme ck-mb) > 3 × ULN.

(18) Fasting triglyceride ≥ 5.64 mmol/L (500 mg/dL).

(19) Blood amylase and lipase levels exceed the upper limit of the normal range and are clinically significant, according to the researchers’ assessment.

(20) Other factors and laboratory outliers of clinical significance that the investigators believe may interfere with interpreting the efficacy and safety data in this study.

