#### Exit and withdrawal criteria

(1) Pregnant women or women planning for pregnancy.

(2) Intolerable adverse events.

(3) Worsening of blood glucose levels.

(4) Severe or repeated hypoglycemia.

(5) Pancreatitis.

(6) Participants who do not take medication nor accept testing as required.

(7) Participants who cannot complete the study as planned or have other factors that may affect the efficacy or safety evaluation.

(8) Participants who participate in other clinical trials during the trial.

(9) Participants who voluntarily withdraw from the study with informed consent.

(10) Participants who do not explicitly raise the request to withdraw from the test but no longer accept medication, testing, and follow-up.

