### Randomisation and interventions

A total of 184 participants will be randomly allocated to receive either canagliflozin or metformin treatment (1:1). The randomization operation will be generated by an independent statistician, who will ensure the balance of participants according to age, sex, HbA1c and BMI and course of their disease when grouping, and a code list will be directly allocated to the main investigators of every center. The intervention content of the two groups is as follows.

Canagliflozin treatment group: For oral treatment, the participants will receive canagliflozin tablets (Janssen-Cilag S.p.A., Ltd., National Drug Approval: H20170375) once daily, 100–300 mg per time, with a minimum dose of 100 mg per day and maximum dose of 300 mg per day.Metformin treatment group: For oral treatment, the participants will receive metformin hydrochloride tablets (Sino-American Shanghai Squibb Pharmaceutical Co., Ltd., National Drug Approval: H20023370 (0.5 g × 20 tablets)/Sino-American Shanghai Squibb Pharmaceutical Co., Ltd., National Drug Approval: H20023371 (0.85 g × 10 tablets × 2 plates)), 1–3 times a day, 500–2000 mg per time, with a minimum dose of 500 mg per day and maximum dose of 2550 mg per day.

Regarding weekly titration for oral drug metering, the titration targets are fasting blood glucose (FBG) (3.9–5.6 mmol/L) and blood glucose at 2 h after each of the three meals (5.0–7.0 mmol/L). After meeting the above criteria, the participants will continue the medication for 3 months and then stop.

Routine diabetes health education will be provided to all participants during the treatment period. Routine diet control and appropriate exercises will be planned. Follow-up will be conducted monthly for the first 3 months after the end of treatment and every 3 months thereafter for 1 year (Table 1; Fig. 2). Participants with FBG > 7.0 mmol/L and postprandial blood glucose (PBG) > 10 mmol/L during the follow-up period are defined as having hyperglycemia recurrence, which will be treated according to the Chinese guidelines for the diagnosis and treatment of T2DM and is defined as not remitted.

**Table 1 Tab1:** Participant visit schedule

**Research Stage**	**Screening**	**Baseline**	**Intervention Period**				**Follow-up Period**		

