### Outcomes

#### Primary outcome

Remission rates.

This is the percentage of participants in each group who meet the remission criteria during follow-up: HbA1c < 6.5% maintained for > 3 months after the treatment discontinuation [27].

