### Sample size calculation

This is a controlled trial aims at exploring the remission effect of canagliflozin on T2DM. The experimental group is the canagliflozin group, and the control group is the metformin group. The main observation index is the remission rate. We referred to relevant studies and set the remission rate for metformin as 20.9%, similarly the estimated remission rate of canagliflozin was also 20.9%. For non-inferiority design, the cut-off value was 2%, α = 0.025, and power = 0.80. The sample size calculated by PASS 15 software was 73 cases in each group, and at least 92 participants should be enrolled in each group at baseline, for a total of 184 participants.

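### Exit criterion 7 allows randomised participants to leave for unspecified factors that may affect the efficacy evaluation, so in this open-label trial primary outcomes can be lost selectively by arm

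*Protocol article*

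**What the plan says.** Under Exit and withdrawal criteria, item 7 reads "Participants who cannot complete the study as planned or have other factors that may affect the efficacy or safety evaluation". It lists no factors, names no decision maker and asks for no blinded or independent judgement. Item 3 of the same list is "Worsening of blood glucose levels".

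A very similar catch-all stands among the exclusion criteria, item 20: "Other factors and laboratory outliers of clinical significance that the investigators believe may interfere with interpreting the efficacy and safety data in this study". That one applies at screening and gives the judgement to the investigators.

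On blinding, Study design says "This is a multicenter, parallel-group, randomized controlled, open-label trial". Randomisation and interventions adds that "a code list will be directly allocated to the main investigators of every center".

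The primary outcome is "HbA1c < 6.5% maintained for > 3 months after the treatment discontinuation", so it can be observed only in people who are still measured well after the drug has stopped. Randomisation and interventions says of hyperglycaemia recurrence during follow-up that it "is defined as not remitted". The article gives no such rule for someone who exits on another ground. Data analysis plans multiple imputation for missing values, with sensitivity analyses that are not described.

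**The concern.** Most other items on the exit list describe an event or act: pregnancy, an adverse event, hypoglycaemia, pancreatitis, non-adherence, joining another trial, withdrawn consent, silent drop-out. The second half of item 7 differs. Its ground is that something about the participant might influence the efficacy result. At screening such a judgement does not harm the comparison, because it precedes allocation. After randomisation in an open-label trial, it can be made with the drug and the glucose course in view, since Follow-up visit has participants reporting glucose weekly during titration.

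If such exits are related to prognosis and differ between arms, the groups that supply outcomes are no longer the groups that were randomised. An objective endpoint such as HbA1c protects the measurement. It does not protect the choice of who is measured.

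**Working it through.** **Inputs from the Protocol article.** Sample size calculation gives a remission rate of 20.9% in both arms, a 2% cut-off, α = 0.025, power 0.80, 73 per group, and 92 per group enrolled.

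**The plan's own figures.** With p = 0.209 in both arms and margin d, n per arm = (1.960 + 0.842)² × 2p(1 − p)/d².
- d = 0.02: 7.849 × 0.3306/0.0004 ≈ 6,488, not 73.
- d = 0.189 (which equals 0.209 − 0.02): 7.849 × 0.3306/0.0357 ≈ 72.7, rounded up to 73.
- From 73 to 92: 73/0.8 = 91.25, rounded up to 92. This implies an allowance of about 20%, which the article does not state, or 92 − 73 = 19 people per arm.

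The mismatch on 73 is a separate matter. This point does not depend on it, but it makes the 2% figure a poor yardstick.

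**Illustration of selective exit.** Assumptions: the true rate is 20.9% in both arms, 92 are randomised per arm, k people leave one arm and none leave the other, all k are non-remitters, and only those remaining are analysed. The value of k is assumed, from 5 to 19, where 19 is the loss that the plan itself allows for.

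Expected remitters per arm: r = 0.209 × 92 = 19.228. Observed rate in the depleted arm: r/(92 − k).

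| k | Rate in depleted arm | False difference | Rejection rate, two-sided 0.05 |
|---|---|---|---|
| 0 | 20.9% | 0 | 5.0% |
| 5 | 19.228/87 = 22.1% | 1.2 points | 5.4% |
| 10 | 19.228/82 = 23.4% | 2.5 points | 6.9% |
| 19 | 19.228/73 = 26.3% | 5.4 points | 13.2% |

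The rejection rate is the normal approximation Φ((δ − 1.96·SE₀)/SE₁) + Φ((−δ − 1.96·SE₀)/SE₁), where δ is the false difference, SE₀ the pooled and SE₁ the unpooled standard error. For k = 10: δ = 0.0255, SE₀ = 0.0630, SE₁ = 0.0631, giving 0.060 + 0.009 = 0.069.

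**What imputation does to this.** Suppose the imputation model gives the k exits an average remission probability q. The arm's estimate becomes (r + kq)/92, so the bias is kq/92. For k = 10:
- If the model knows nothing about why they left, q equals the rate among those remaining, 0.234. The bias is 10 × 0.234/92 = 2.5 points, the same as without imputation.
- If the recorded data lower q to 0.10 (an assumed value), the bias is 10 × 0.10/92 = 1.1 points.
- If the recorded data identify all ten as non-remitters, q = 0 and the bias is 0.

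**The case against.** The best defence has four parts.

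1. **Item 7 does not state the consequence.** It does not say that HbA1c measurement stops, that the participant leaves the analysis, or who decides. An article may leave those details to the full protocol. This stands in part. A reader might infer that unblinded investigators may remove anyone they choose and drop them from the analysis, but the article does not say so. That the investigator decides is an inference from exclusion criterion 20 and the open-label design. What the article does state is a ground for exit, tied to the efficacy evaluation, that operates after randomisation. That is enough for the point.

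2. **The plan imputes.** A shrinking denominator is not the stated analysis, so the table is an illustration and not a forecast. Much of what an investigator sees is also recorded, in glucose reports and participant diaries, and an exit that depends only on recorded data can be handled by an imputation model that uses those data. This stands, and it narrows the problem. It does not remove it, because an open-ended judgement need not rest on recorded data alone.

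3. **Failures are already counted.** The rule on recurrence does close part of the route. It covers only glucose recurrence during follow-up, and so not an exit before recurrence.

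4. **Item 3 is the more direct outcome-related exit.** That is correct, and the fix must address it too. It does not make item 7 sound.

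A reader might also infer that eight such exits would exceed the whole 2% cut-off. That holds only from a base of 73 (15/73 = 20.5% to 15/65 = 23.1%), and 73 is the number left after the allowance for loss, so loss is counted twice. From 92 randomised, 19/92 = 20.65% becomes 19/84 = 22.62%, a shift of 1.97 points.

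**Conclusion.** The point holds as a weakness in a stated rule. Item 7 opens a discretionary, outcome-related exit after randomisation in an open-label trial, and nothing in the article fully closes it. It should be changed, since the same clause already does its legitimate work at screening.

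The size is conditional. Under the one-sided scenario above, 5 to 19 exits produce a false difference of about 1.2 to 5.4 points and a rejection rate of about 5.4% to 13.2% in place of 5.0%. The upper end needs the entire allowance of 19 to be non-remitters from one arm. Exits that are balanced between arms or unrelated to outcome would give less, and imputation that uses the reasons for exit would reduce the bias, at best to zero. The documents do not support the stronger reading that bias will occur or that the planned analysis is already invalid.

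**What to change.** Remove from item 7 the catch-all about factors that may affect the efficacy evaluation, as a ground for leaving the study after randomisation. Keep it at screening, in exclusion criterion 20. When such a factor arises later, log it as a protocol deviation, keep the participant in the follow-up and HbA1c measurement already scheduled, and analyse the participant in the randomised arm.

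Say explicitly that stopping treatment and leaving the study are different things. Any stopping of treatment for safety stays as the protocol has it, and it does not end outcome follow-up unless consent is withdrawn. Reconcile exit criterion 3 on worsening glucose with the rule in Randomisation and interventions that counts recurrence as not remitted, so that the two passages lead to one handling of the outcome.

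The cost is a change of wording and a deviation-log entry, with no visits beyond those scheduled. The downside is that some participants with deviations stay in the analysis, which may slightly dilute the treatment contrast.

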### Participant recruitment

The recruitment period of this study will start in December 2023. Participants will be invited to participate in the study through meetings, electronic and social media. The recruitment will end on 31 December 2025.

### Randomisation and interventions

A total of 184 participants will be randomly allocated to receive either canagliflozin or metformin treatment (1:1). The randomization operation will be generated by an independent statistician, who will ensure the balance of participants according to age, sex, HbA1c and BMI and course of their disease when grouping, and a code list will be directly allocated to the main investigators of every center. The intervention content of the two groups is as follows.

Canagliflozin treatment group: For oral treatment, the participants will receive canagliflozin tablets (Janssen-Cilag S.p.A., Ltd., National Drug Approval: H20170375) once daily, 100–300 mg per time, with a minimum dose of 100 mg per day and maximum dose of 300 mg per day.Metformin treatment group: For oral treatment, the participants will receive metformin hydrochloride tablets (Sino-American Shanghai Squibb Pharmaceutical Co., Ltd., National Drug Approval: H20023370 (0.5 g × 20 tablets)/Sino-American Shanghai Squibb Pharmaceutical Co., Ltd., National Drug Approval: H20023371 (0.85 g × 10 tablets × 2 plates)), 1–3 times a day, 500–2000 mg per time, with a minimum dose of 500 mg per day and maximum dose of 2550 mg per day.

Regarding weekly titration for oral drug metering, the titration targets are fasting blood glucose (FBG) (3.9–5.6 mmol/L) and blood glucose at 2 h after each of the three meals (5.0–7.0 mmol/L). After meeting the above criteria, the participants will continue the medication for 3 months and then stop.

Routine diabetes health education will be provided to all participants during the treatment period. Routine diet control and appropriate exercises will be planned. Follow-up will be conducted monthly for the first 3 months after the end of treatment and every 3 months thereafter for 1 year (Table 1; Fig. 2). Participants with FBG > 7.0 mmol/L and postprandial blood glucose (PBG) > 10 mmol/L during the follow-up period are defined as having hyperglycemia recurrence, which will be treated according to the Chinese guidelines for the diagnosis and treatment of T2DM and is defined as not remitted.

**Table 1 Tab1:** Participant visit schedule

**Research Stage**	**Screening**	**Baseline**	**Intervention Period**				**Follow-up Period**		
			**Start of treatment**	**Dose titration period** **(weekly)**	**Maintenance treatment** **(monthly)**	**Drug discontinuance**	**First three months** **(monthly)**	**Last nine months** **(every three months)**	**End of the follow-up**
Informed consent		**×**	**×**	**×**	**×**	**×**	**×**	**×**	**×**
Participant information		**×**	**×**	**×**	**×**	**×**	**×**	**×**	**×**
Medical history		**×**	**×**	**×**	**×**	**×**	**×**	**×**	
Clinical examination		**×**	**×**	**×**	**×**	**×**	**×**	**×**	
Inclusion and exclusion criteria		**×**	**×**	**×**	**×**	**×**	**×**	**×**	**×**
Assignment filter number		**×**	**×**	**×**	**×**	**×**	**×**	**×**	**×**
Weight, height, and BMI									
Body composition	**×**		**×**	**×**	**×**		**×**	**×**	
Waist circumference									
Blood pressure and resting heart rate									
HbA1c, FPG, 2hPG			**×**	**×**	**×**		**×**		
FCP, 2hCP, FINS, INS-2 h	**×**		**×**	**×**	**×**		**×**		
Blood biochemistry, blood routine			**×**	**×**	**×**		**×**		
Thyroid function		**×**	**×**	**×**	**×**	**×**	**×**	**×**	**×**
Routine urine, urine microalbumin			**×**	**×**	**×**		**×**		
ECG, UCG		**×**	**×**	**×**	**×**	**×**	**×**	**×**	**×**
Abdominal ultrasonography	**×**		**×**	**×**	**×**	**×**	**×**	**×**	
Eye-ground photography, electromyography, color doppler ultrasound of blood vessels of the neck and lower limbs	**×**		**×**	**×**	**×**	**×**	**×**	**×**	
Stored samples (blood and stool)	**×**		**×**	**×**	**×**		**×**	**×**	
DSQLS、SDSCA	**×**		**×**	**×**	**×**		**×**	**×**	
Medication, diet, and exercise guidance	**×**								
Treatment of comorbidity	**×**								
Blood glucose monitoring	**×**	**×**							
Dietary and sport record	**×**	**×**							
Occurrence of hypoglycemia, ketosis, and other adverse reactions	**×**	**×**							
Distribute participant diaries		**×**	**×**	**×**	**×**	**×**	**×**	**×**	
Recall and review participant diaries	**×**	**×**	**×**	**×**	**×**	**×**	**×**	**×**	

BMI, body mass index; ECG, electrocardiograph; FCP, fasting C-peptide; FINS, fasting serum insulin; HbA1c, glycosylated hemoglobin A1c; 2hCP, 2 - hour postprandial C-peptide; INS-2 h, 2 - hour postprandial insulin; DSQLS, diabetes specific quality of life scale; SDSCA, summary of diabetes self care activities; UCG, ultrasonic cardiogram

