#### Biochemical measures

Participants will be required to fast at least 10 h before the study visit and return to the center between 6 and 10 am. They will be instructed to stop smoking and abstain from caffeine and alcohol 10 h before the study visit to ensure that all fasting blood samples are collected before taking medication in the morning. Biochemical tests, such as hematuria, will be completed at each center, and stool and blood samples of each participant will be collected and sent to professional institutions for the subsequent intestinal flora and metabolomics testing.

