### Data analysis

All statistical analyses will be performed by full-time statisticians using R Studio (Version 1.2.5001, R Studio Inc., Boston, MA, USA). The normality test will be used to determine whether the data are normally distributed. Continuous variables with a normal distribution will be reported as the mean ± SD, and ordinal and non-normally distributed variables will be reported as the median and interquartile range. Independent samples t-tests or Mann-Whitney U-tests will be used for comparisons, as appropriate. Categorical variables will be reported as counts and proportions, and the Pearson χ^2^ test or Fisher’s exact test will be used for comparisons, as appropriate.

The primary outcomes (remission rate 3 months after drug withdrawal and after 1 year of follow-up) will be compared between groups using Pearson’s χ^2^ test or Fisher’s exact test. Logistic regression will be used to adjust for potential confounders. Variables with P < 0.05 in the univariate comparisons, and known confounders that could impact the efficacy, will be included in the multivariable logistic regression models.

Subgroup analyses will be conducted of the primary outcomes stratified by age group (young, 18 ~ 35 years; middle-aged, 36 ~ 59 years; older, 60 ~ 65 years); duration of disease (<1 year, 1 ~ 2 years, 2 ~ 3 years); BMI (18.5 ~ 27.9 kg/m^2^, 28 ~ 40 kg/m^2^); and sex, using the same methods of analysis.

For the secondary outcomes, continuous data will be analyzed using the linear mixed effects model, which will use the random intercept model to explain the internal correlation of participants. Discontinuous data will be analyzed similar, but the generalized linear model appropriate to the distribution assumptions and link functions will be used. The analysis of all secondary outcome indicators also corrected for potential confounders (including variables with P < 0.05 in the univariate comparisons and known confounders that could have an impact on the efficacy). The safety indicators will be analyzed using the same methods used to analyze the main outcome indicators.

Missing values will be filled using multiple imputation methods, and sensitivity analyses will be performed.

Two-tailed P-values will be used, and P-values < 0.05 will be regarded as statistically significant. Point estimates will be reported with 95% confidence intervals.

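### Centre is missing from the stated balancing factors and from every named analysis of this six-hospital trial; the cost is some precision, not bias

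*Protocol article*

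**What the plan says.** All references are to the protocol article.

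- **Study design** names six participating hospitals.
- **Primary outcome** defines remission by a cut-off: "HbA1c < 6.5% maintained for > 3 months after the treatment discontinuation".
- **Biochemical measures**: "Biochemical tests, such as hematuria, will be completed at each center". Only stool and blood samples are described as leaving the centres, "sent to professional institutions for the subsequent intestinal flora and metabolomics testing". No central laboratory for HbA1c is mentioned.
- **Randomisation and interventions**: an independent statistician is described as the one "who will ensure the balance of participants according to age, sex, HbA1c and BMI and course of their disease when grouping". Five factors are listed and centre is not one of them. On how the sequence reaches the hospitals, the section says only this: "a code list will be directly allocated to the main investigators of every center". Whether each centre receives its own balanced list is not said.
- **Data analysis**: the primary outcomes "will be compared between groups using Pearson’s χ^2^ test or Fisher’s exact test". An additional logistic regression takes variables that pass a univariate significance screen, plus confounders described as known but not listed. Secondary continuous outcomes use a mixed model "which will use the random intercept model to explain the internal correlation of participants". The subgroups are age, disease duration, BMI and sex. Centre appears in none of these.

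**The concern.** A yes/no endpoint cut from a laboratory value is sensitive to small calibration differences, because a modest offset carries people across 6.5%. Six hospitals that run their own assays and give their own lifestyle guidance will probably differ in remission rate. A design that neither balances nor models centre leaves those differences as unexplained noise in the arm comparison and lets the arms differ in centre mix by chance. A design that balances centre through separate lists but ignores it in the analysis has the opposite fault: the standard error is larger than it need be. What is at stake is efficiency in a trial of only 184 people, and an analysis that matches the way allocation was done.

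**Working it through.** **Inputs from the article.** Six centres; N = 184, 92 per arm, 1:1; remission 20.9% (Sample size calculation).

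**Inputs assumed.** The article gives no centre spread, HbA1c SD or centre sizes. Assumed: off-drug HbA1c SD 0.9; laboratory offset SD 0.1, 0.2 or 0.3 HbA1c points; centre effects normal on the logit scale with SD 0, 0.5, 1.0 or 1.5; centre sizes 60/40/30/24/18/12 (step 3) or near-equal (step 4).

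The article states no figure about centre, so there is none to reproduce.

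**1. Effect of one laboratory's offset on its own rate.** z = Φ⁻¹(0.209) = -0.81. An offset of 0.2 gives Φ(-0.81 - 0.2/0.9) = 15.1% or Φ(-0.81 + 0.2/0.9) = 27.8%. On the logit scale, ln(0.209/0.791) = -1.33, ln(0.151/0.849) = -1.73 and ln(0.278/0.722) = -0.95. The shift is therefore about 0.39, and a laboratory offset SD of 0.2 corresponds to a centre logit SD of about 0.4.

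**2. Ordinary sampling error of the arm difference.** √(2 × 0.209 × 0.791 / 92) = 0.060, or 6.0 points.

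**3. Chance centre mix under unstratified allocation.** In 4,000 simulated trials the arm difference due to centre mix alone had SD 0.42, 0.85 and 1.26 points at offset SD 0.1, 0.2 and 0.3. At 0.2, its share relative to the sampling variance is (0.85/6.0)² = 2%.

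**4. Operating characteristics.** Simulation with 6 near-equal centres, two-sided 5% test, and an assumed odds ratio of 2.72 (log-odds 1.0) for power. In an average centre that is 20.9% against 41.8% (odds 0.264 × 2.72 = 0.718; 0.718/1.718).

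| Centre logit SD | 0 | 0.5 | 1.0 | 1.5 |
|---|---|---|---|---|
| Type I: unstratified lists, chi-square | 5.2% | 5.1% | 5.2% | 4.5% |
| Type I: lists by centre, chi-square | 5.2% | 4.7% | 4.2% | 2.7% |
| Type I: lists by centre, CMH | 5.2% | 5.0% | 5.5% | 4.8% |
| Power: unstratified lists, chi-square | 86% | 84% | 77% | 66% |
| Power: unstratified lists, CMH | 85% | 85% | 81% | 77% |
| Power: lists by centre, chi-square | 86% | 84% | 78% | 65% |
| Power: lists by centre, CMH | 86% | 85% | 82% | 76% |

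Only the gap between rows within a column measures the cost of ignoring centre. Power falls along every row because the odds ratio is held fixed while the centres spread out.

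- With no true effect, the mean arm difference stayed within about 0.2 points of zero in every setting.
- The SD of the arm difference at logit SD 1.0 was 6.33 points unstratified and 5.98 stratified. Centre contributes √(6.33² - 5.98²) ≈ 2.1 points. At 0.5 it contributes √(6.09² - 5.98²) ≈ 1.1 points.
- Further runs gave no power gain at logit SD 0.4 (86% both ways), a gain of about 3 points at 0.5 (1 in the table), and about 5 at 1.0. With lists by centre and an unstratified test, type I error at 1.0 was about 3.7% (4.2% in the table). The spread between runs is simulation error, so the gain at 0.4 to 0.5 is best read as 0 to 3 points.
- Most of the gain comes from the analysis. At logit SD 1.0, CMH alone lifts power from 77% to 81%; balancing alone lifts it to 78%.

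**The case against.** **The article is condensed.** Centre terms are often left to a full protocol or analysis plan, neither of which is shown. That is fair for detail, and it is why the point says centre is not named rather than excluded. But the article does commit to a particular list of balancing factors, a particular primary test and a particular random effect. The point is about those stated choices.

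**The text leaves two openings.** A code list goes to every centre, which may mean one list per centre. The logistic model also admits known confounders, which could include centre. Both stand as openings. The first would remove the allocation half of the point but leave an unstratified test on a stratified design. The second does not reach the primary chi-square or Fisher comparison.

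**Local HbA1c reading is inferred.** The sentence on local testing does not name HbA1c. This stands. The inference is the natural one, since only flora and metabolomics samples are said to go elsewhere.

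**The effect is small.** At the laboratory offsets considered, this largely stands: centre mix adds about 2% relative to the sampling variance, and the power gain is near nil at logit SD 0.4. The 5-point and larger losses need differences in care or case mix on top of assay offsets.

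**The tempting stronger reading** is that laboratory differences leak into the treatment effect as bias. The documents do not support it. Every hospital contributes to both arms under 1:1 randomisation, and the unadjusted test kept its type I error at about 5% or below.

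A reader might also set the centre contribution against the 2% cut-off in Sample size calculation and call it decisive. That comparison misleads. With 20.9% in both arms, a 2-point margin would need 2 × 0.209 × 0.791 × (1.96 + 0.84)² / 0.02² ≈ 6,488 per group against the 73 stated, and Data analysis never uses the margin. Sampling error alone is three times as large. That discrepancy is a separate matter.

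**Conclusion.** The point holds as one of efficiency and of matching the analysis to the allocation. As stated, the plan neither balances nor analyses by centre in a six-hospital trial whose endpoint is probably read locally. If the lists are not by centre, the cost is chance imbalance and about 0 to 3 power points at centre logit SD 0.4 to 0.5, about 5 at 1.0 and about 10 at 1.5. If they are by centre, the stated test is slightly conservative, at about 4% instead of 5% at logit SD 1.0. There is no bias and no inflated type I error under either reading. All sizes rest on assumed centre spread, HbA1c SD, centre sizes and odds ratio; none of these is in the documents. The change is worth making because it is cheap and correct whichever way the code lists work, not because the result would otherwise be unsound.

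**What to change.** 1. Replace the unstratified primary test with a CMH test stratified by centre, and report the centre-stratified (Mantel-Haenszel) risk difference with its 95% confidence interval.
2. Add centre as a fixed effect to the secondary mixed models, alongside the participant random intercept.
3. State whether the code lists are separate and balanced by centre. If they are not, balance allocation by centre.
4. State where HbA1c is assayed.

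**Cost.** N does not change. A rule for merging very small centres must be written in advance. The mixed models spend up to five degrees of freedom. Balancing by centre is easy under minimisation. Under stratified lists, six centres on top of five existing factors would be too sparse for 184 people, so another factor may have to be dropped or coarsened. For remission, CMH is preferable to five centre terms in the logistic model: only about 0.209 × 184 ≈ 38 remissions are expected, and that model already carries other covariates. If centre spread turns out to be nil, CMH costs at most about 1 power point (86% against 85% with unstratified lists).
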